#### Qualitative analyses

Data from the in-depth interviews will be transcribed and translated prior to content analysis. Content analyses will identify emergent themes related to participants’ experiences with the intervention components that each received, how they utilized the skills learned in the intervention, and the impact that participation in the intervention had on their lives. Data will be analyzed using NVivo software, aided by group discussions to reach consensus on themes identified.

#### Cost-effectiveness analyses

Cost-effectiveness of the intervention will be analyzed based on STI infections and number of HIV and HCV cases averted over the 12-month period. We will compare cost-effectiveness of HIVRR+MF to HIVRR, using the cost of staff time, supplies, and overhead for the HIVRR and the MF interventions. We will calculate the incremental cost-effectiveness ratio between treatment *i* (HIVRR + MF) and *j* (HIVRR) in terms of outcome *k* by comparing extra cost with extra effectiveness in paired combinations: *ICERijk* = (*Ci* – *Cj*)/(*Eik* – *Ejk*) where *Ci* and *Cj* are the costs and *Eik* and *Ejk* are the effectiveness measures for treatments *i* and *j* measured along output *k*. This approach safeguards validity against any biased measurements of cost or effectiveness that are common to both *i* and *j* because they cancel out. Policymakers can easily and directly compare *ICERijk* to their existing costs and cost-effectiveness metrics to assess the added benefit of the microfinance intervention. We will also report total cost-effectiveness ratios for each intervention: *CERik* = *Ci/Eik*. To construct an effectiveness outcome of HIV, STIs, and HCV transmissions averted, we will use standard modeling procedures reported in HIV cost-effectiveness literature; i.e., a Bernoulli Process Model, the difference in risk-behavior frequencies times HIV transmission probabilities per act [31, 32]. One-way sensitivity analyses will use a range (e.g., 95% CIs) of HIV and HCV rates in the target population that may be compared to results to assess the robustness of estimates. Policymakers may compare the HIV, STIs, and HCV cost-effectiveness ratio to ratios for existing HIV interventions [31, 32] to ascertain the potential value of the microfinance intervention.

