**Fig. 1 Fig1:**
[figure not shown]
Theoretical framework

**Table 1 Tab1:** Assessment variables

	Measurement	Timepoint^a^			
Moderators		B	M6	M9	M15
Age, income, education, marital status, experience of sex work, trauma	Sociodemographic Questionnaire	X	X	X	X
Substance abuse and criminal justice history	Modified Risk Behavior Assessment (RBA) [36]	X	X	X	X
Mental health status	BSI [37]	X	X	X	X
Partner violence history (paying and intimate)	Revised Conflict Tactics Scale [38]	X	X	X	X
Number and type of sexual partners (past year)	Modified RBA [36]	X	X	X	X
Perceived stigma	Modified Sex Worker Stigma (SWS) Index [39]	X	X	X	X
Mediators		B	M6	M9	M15
HIV/STI knowledge	HIV/STI knowledge [40]	X	X	X	X
Condom use self-efficacy	Condom Use Self-Efficacy Scale [41]	X	X	X	X
Condom use outcome expectancies	Condom Barriers Scale [42]	X	X	X	X
Condom negotiation self-efficacy	Condom Negotiation Self Efficacy Scale [43]	X	X	X	X
Sexual communication skills	Sexual Communication Scale [44]	X	X	X	X
Social support	MSPSS [45]	X	X	X	X
Current partner violence (paying and intimate)	Revised Conflict Tactics scale [38]	X	X	X	X
Access to services	RBA Services [36]	X	X	X	X
^b^Financial literacy	Financial literacy knowledge [46]	X	X	X	X
^b^Savings deposits	Bank Statements		X	X	X
^b^Vocational training sessions attended	Attendance/process		X	X	X
Outcomes		B	M6	M9	M15
STI (gonorrhea, syphilis, trichomoniasis, chlamydia, *Mycoplasma genitalium*), HCV, and HIV status	Laboratory assays (see Table 2)	X		X	X
Sexual behavioral risk: number and % of unprotected sexual acts	Modified RBA [36]	X	X	X	X
Number and % shared injection acts, other drug use	Modified RBA [36]	X	X	X	X
Proportion of income from sex work, savings, debt	Economic Indicators Questionnaire	X	X	X	X
Cost of staff time, supplies, overhead for HIVRR and for MF	Project records; Administration review	Ongoing			

^a^*B* baseline (prior to randomization or intervention); *M6* month-6 follow-up, *M9* month-9 follow-up, *M15* month-15 follow-up

^b^Uniquely associated with asset theory and the HIVRR+MF arm

*HCV* hepatitis C virus, *HIV* human immunodeficiency virus, *HIVRR* HIV relative risk, *MF* microfinance, *STI* sexually transmitted disease

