### Intervention

All participants receive four HIVRR sessions and those assigned to the combination HIVRR+MF treatment arm receive an additional 30 sessions, including (1) six training sessions focused on financial literacy, (2) 24 sessions of vocational training in hairdressing, sewing, or manicurist professions, as well as (3) a matched savings program which incentivizes them to accumulate assets for small business development or job/vocational training. The NOVA intervention period lasts a total of 3 months post randomization, with intervention activities lasting for 2 weeks in the control arm, and for the full 3 months in the treatment arm. A brief description of each intervention component is provided below:

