#### Vocational Training (VT)

During months 2 and 3 of the intervention period, the treatment arm receives the Vocational Training (VT) intervention component. VT provides technical education and skills-building in a craft or trade. Including VT as a component in the HIVRR+MF intervention arm allows participants to gain competence in an employable trade, which grounds the intervention in the real world for scale-up after the trial ends. Participants in the treatment arm decide whether they wish to be enrolled in hairdressing, sewing, or manicurist vocational training sessions (dependent on course availability at each study site). Our selection of these options was informed by local feedback and a feasibility pilot conducted prior to study start, which confirmed that these were considered growing small business targets for women and that high-risk women reacted favorably to this model of vocational training. These trainings are conducted by professionals, who work either individually in the community or through a school or training program. VT partner sites were selected based on the quality of their facilities, the availability of afternoon and part-time training hours to accommodate participant schedules, and a reputation for successful graduation and certifications among students. All treatment arm participants are eligible to attend VT sessions regardless of how many FLT sessions they attended, as the material presented in the VT sessions is unrelated to the FLT. Vocational training is provided three times per week over the course of 2 months, for 24 sessions. Tuition is free to participants and women attend in small groups with only their cohort peers. Participants receive small financial incentives (US$12) for sessions attended.

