#### Matched savings

From week 3 until the end of the intervention period at the end of month 3, the treatment arm receives the matched savings component of the intervention. The matched savings component of the HIVRR+MF intervention is also adapted from the Undarga program [17]. Building assets prior to shifting sources of income or moving to new or self-employment may increase the likelihood for increased income from other sources than sex work. As mentioned above, participants receive incentive payments (US$12/session) for each FLT or VT session attended. During the FLT intervention, participants receive support to open a personal savings account in a partner bank, and are encouraged to deposit their session attendance incentives in this account. Throughout the rest of the treatment intervention period, for every dollar of their incentive payment money deposited in their personal account, the project will deposit an equal amount in a separate, project-controlled account under the participant’s name. Participant’s funds will only be matched up to the total amount that they have received from incentive payments for session attendance – this limit ensures that women are not earning income through sex work for their matched savings. If a participant decides to save 100% of her incentive after every session, she will have saved a total of US$360 and would receive a matching US$360 for a total of US$720. Due to lack of documentation, lingering distrust of the banking system, or other barriers, some women may elect to never open a bank account. These participants have the option to store money with the program staff in an informal account until the time of withdrawal, and these informal accounts are also matched in a separate, project-controlled account under the participant’s name.

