#### Assessments

Baseline and follow-up assessments are administered by research assistants in project field office locations. Assessments take place at a pre-intervention baseline (prior to cohort assignment and randomization), then at 6, 9, and 15 months after randomization and intervention session 1 (which occur simultaneously, as participants are randomized as a cohort immediately prior to beginning the first intervention session). Since the HIVRR+MF treatment arm receives an intervention that is approximately 2.5 months longer than the control arm, we allocated an additional 2.5 months of follow-up time for in the control arm. Behavioral questionnaires are utilized at all assessments, and biological testing procedures are conducted at baseline, month-9 and month-15 assessments.

Behavioral questionnaires are conducted using computer-assisted self-interviewing (CASI) methods, with the same survey tool that the research assistants use to assess study eligibility and which can be completed in approximately 2 h. The baseline behavioral questionnaire addresses the main outcome variables of interest to the study (number of partners, number of sex acts, number of sex acts which are unprotected, number of paying partners, incidences of drug use, incidences of injection drug use and incidences of risky injection behaviors) in addition to several of the theoretical constructs underlying the study (self-efficacy in a number of risk-reduction behaviors, outcome expectancies and risk-reduction intentions) and a number of potential moderators (demographics, financial status, experience of IPV and gender-based violence (GBV), social support, linkage to care and service utilization). Table 1 contains a list of the specific measures used for each construct.

Follow-up assessments occur as early as 1 week before the exact follow-up date, and as late as 3 weeks after the exact follow-up date. Like the baseline behavioral questionnaire, the follow-up behavioral questionnaires address the main outcome variables, moderators and mediators of interest to the study. The follow-up questionnaires also include additional questions to assess how HIVRR+MF participants have utilized the vocational training and financial literacy training that they have received.

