#### Qualitative assessment

To help us open the “black box” of HIVRR+MF delivery, we conduct semi-structured, in-depth interviews at three points in time during study implementation: at 1 month, 3 months and 15 months post randomization and session 1 (corresponding to the end of the financial literacy sessions, vocational trainings sessions for HIVRR+MF participants, and to the month-15 follow-up assessment for all participants). We randomly select one participant from each cohort (approximately 50 women) to complete interviews. Questions focus on participants’ perception of the intervention, their experience with both the HIV-risk reduction and microfinance components and their reaction to the various role-plays, activities and goal-setting assignments, as well as the reactions or interactions with family, friends, colleagues related to their participation, factors promoting the use of the session information and skills and barriers impeding participation. Importantly, questions also focus on perceptions of how the intervention influenced participant safety, including any policy involvement, stigma or discrimination, drug use before and during the intervention, and savings and the potential access to matched savings, and alternative income sources. All interviews are audio-taped, transcribed and translated to English.

Cost-effectiveness is measured through a series of staff questionnaires, asking project staff about the time they spend on various intervention activities, along with budgets and financial records.

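### The cost list for the cost-effectiveness analysis names none of the payments specific to HIVRR+MF (session incentives, match, vocational tuition), so the incremental cost as written is understated

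*Protocol article*

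**What the plan says.** The Cost-effectiveness analyses section of the protocol article defines the ICER as (Ci − Cj)/(Eik − Ejk), with costs obtained "using the cost of staff time, supplies, and overhead for the HIVRR and the MF interventions". Table 1 lists the cost variable as "Cost of staff time, supplies, overhead for HIVRR and for MF". The Qualitative assessment section describes the data collection as staff questionnaires, "asking project staff about the time they spend on various intervention activities, along with budgets and financial records".

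The intervention sections describe payments outside those three categories:

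- Under Intervention, "those assigned to the combination HIVRR+MF treatment arm receive an additional 30 sessions": six on financial literacy and 24 of vocational training. Each carries a US$12 attendance incentive.
- Under Matched savings, a woman who saves every incentive accumulates US$360 and "would receive a matching US$360 for a total of US$720". The project pays its half of a qualifying purchase directly to the vendor, up to the month-9 assessment.
- Under Vocational Training, outside professionals or schools do the teaching. "Tuition is free to participants and women attend in small groups with only their cohort peers".

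On the time frame, effectiveness rests on STIs and the "number of HIV and HCV cases averted over the 12-month period", while "biological testing procedures are conducted at baseline, month-9 and month-15 assessments". The same section builds averted transmissions with a Bernoulli process model driven by risk-behaviour frequencies. Its only stated sensitivity analysis varies HIV and HCV rates.

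**The concern.** The microfinance component consists largely of transfers and purchased training, yet the list of costs contains neither. The section argues that measurement bias common to both arms cancels in the ICER. That does not help with payments made in one arm only. Nor does it help the planned total ratios CERik = Ci/Eik, which involve no differencing and would also lack the incentives paid for the four HIVRR sessions in both arms.

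Policymakers are told that they can set this ICER directly against their existing costs. A funder who read it that way would see a programme cost without the money handed to participants or paid to trainers. No planned sensitivity analysis touches costs, so the gap would not come to light.

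The 12-month window adds a smaller difficulty. Its start is not given in that section, and the trial follows women for 15 months from randomisation.

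**Working it through.** **1. Inputs (protocol article)**

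- Extra sessions in HIVRR+MF: 6 + 24 = 30 (Intervention).
- Incentive: US$12 per session (Matched savings).
- Match: 1:1, limited to incentives received (Matched savings).
- Assumed STI incidence: 0.144 for HIVRR and 0.043 for HIVRR+MF, with 175 women per arm (Power and sample size).
- Tuition: free to participants, amount not stated (Vocational Training).

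**2. The plan's own figure**

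Incentives: 30 × 12 = US$360. Match: US$360. Total: 360 + 360 = US$720. This agrees exactly with the Matched savings section. The document gives no ICER or cost total, so only the size of the omission can be computed.

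**3. What cancels**

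The HIVRR incentives, 4 × 12 = US$48, occur in both arms and cancel in Ci − Cj at equal attendance. The US$720 has no counterpart in the control arm. The control arm's retention gifts, of unstated value, are also missing from the list and work slightly in the other direction.

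**4. Effect on the ICER for STI**

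Understatement = omitted cost per woman ÷ risk difference, with risk difference 0.144 − 0.043 = 0.101. Because the incidence is of a binary outcome, the unit is a woman with any STI averted, not an STI case.

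| Scenario | Omitted cost per woman | Understatement |
|---|---|---|
| Full attendance, deposit and qualifying spending (ceiling) | US$720 | 720/0.101 ≈ US$7,130 |
| Full attendance, no deposits | US$360 | 360/0.101 ≈ US$3,560 |
| 50% attendance, 50% of incentives deposited and all of the resulting match spent (assumed) | 180 + 90 = US$270 | 270/0.101 ≈ US$2,670 |

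The ceiling for the arm is 720 × 175 = US$126,000. The two stated incidences imply a relative risk of 0.043/0.144 = 0.30, not the stated 0.25. With 0.25 the difference is 0.144 − 0.036 = 0.108, and the ceiling becomes 720/0.108 ≈ US$6,670, so little changes. Tuition comes on top in every row.

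**5. The time window**

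- If the 12 months run from the end of the intervention (months 3 to 15), no biological test falls at month 3. If they run from randomisation, none falls at month 12. Behavioural data come at baseline and months 6, 9 and 15.
- Reading a 15-month risk as a 12-month risk favours the intervention. Under a constant hazard the 12-month risks are 1 − 0.856^0.8 = 0.117 and 1 − 0.957^0.8 = 0.035, a difference of 0.082 against 0.101. The effect would be about 23% too large (0.101/0.082 = 1.23).
- Dropping effects in months 0 to 3 while keeping all costs works against the intervention. The direction is therefore not fixed.

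**The case against.** The strongest reply is that a three-item list in an article is a summary. The list does not say that nothing else counts, the microfinance intervention being costed is itself defined to include vocational training and matched savings, and the stated sources extend to budgets and financial records. Itemised costing is often left to a fuller document. This stands to a degree: a reader might infer that the trial will certainly omit these payments, and the article cannot show that. But it gives the same three categories in two places, and naming a data source does not extend the list of what is to be costed.

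A second reply concerns perspective. None is stated, and from a societal view cash incentives and matches are transfers that may properly be left out. That is correct for those two items. Tuition is a real resource cost under either view, and the comparison offered to policymakers points to a payer view.

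Three stronger readings are not supported:

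- A reader might infer that the 12-month window also makes the ICER favourable. The window has no fixed direction of bias, and because averted infections are modelled from behaviour, the lack of a test at month 3 or month 12 is not decisive. What remains is an undefined window and an unclear mix of observed and modelled cases.
- A reader might infer that all costs fall in the three intervention months. Match spending runs to month 9.
- A reader might infer that these are the programme's largest direct payments. No staff, tuition or overhead figure is given, so this cannot be judged.

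**Conclusion.** The point holds for the cost list. As written, the list understates Ci − Cj by up to US$720 per woman plus tuition, which is at most about US$7,100 per woman with any STI averted on the planned difference and about US$2,700 at the assumed 50% attendance and 50% deposit. If there is benefit, the ICER then looks too favourable.

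This rests on a payer or programme perspective, on reading the list as it stands, and on the protocol's own incidence assumptions. The US$720 is a ceiling that needs full attendance, full deposit and full qualifying spending. The article itself expects some women never to open a bank account, although informal accounts are matched too. A smaller true risk difference would raise the amount per woman averted.

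The undefined 12-month window is a secondary matter of clarity. The analysis serves a secondary aim, so nothing here affects the primary comparison.

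**What to change.** - State the costing perspective: payer or programme for the main analysis, with a societal analysis that excludes cash transfers as a sensitivity analysis if wanted.
- Add to the HIVRR+MF cost the incentives actually paid, the match actually disbursed, and the vocational tuition.
- Add HIVRR session incentives to both arms and retention gifts to the control arm, so that the total ratios are complete as well.
- Vary these costs in sensitivity analysis alongside the HIV and HCV rates.
- Define the start and end of the window and use it for both costs and effects, for example 15 months from randomisation, which contains the match spending to month 9. Say which results use observed cases and which use modelled ones.

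The cost is modest. Attendance, deposits and matched-savings spending are already recorded as process measures, bank statements are listed in Table 1, and tuition should be in the project's financial records. No new data collection from participants is needed. The price is some extra analysis and a less favourable, but more usable, ICER.

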To complement self-reports and utilize an objective assessment measure of risk behavior, we use biological assays to confirm HIV and STI status. We selected five STIs: syphilis, gonorrhea, chlamydia, trichomoniasis and mycoplasma as objective proxies of sexual risk behavior. The choice of these STIs was based on their high prevalence and incidence in this population and the availability of definitive treatment with a single-dose medication (which obviates STI medication treatment adherence and compliance issues). We also selected HCV to index drug-related risk behaviors. A clinical coordinator conducts biological testing in each project field office location. A complete description of test systems used is provided in Table 2.

**Table 2 Tab2:** Biotesting systems used

Infection	Testing specimen	Test system used	Sensitivity (95% CI^a^)	Specificity (95% CI^a^)
HIV	Finger stick (whole blood sample)	Alere Determine™ HIV-1/2 Ag/Ab Combo rapid test system [47]	99.9% (99.4–100.0%)	99.8% (99.5–99.9%)
Hepatitis C (HCV)	Dried blood spot	Murex anti-HCV (version 4.0) [48]	100% (94.79-100%)	99.88% (99.77–99.94%)
Syphilis	Dried blood spot	Murex ICE Syphilis [49]	100% (99.1–100%)	100% (99.2–100%)
Gonorrhea	Vaginal specimen	AmpliSense *N. gonorrhea*/*C. trahomatis*/*M. genitalium*/*T. vaginalis*-MULTIPRIME-FRT PCR [50]	N/A^b^	N/A^b^
Trichomoniasis	Vaginal specimen	AmpliSense *N. gonorrhea*/*C. trahomatis*/*M*. *genitalium*/*T. vaginalis*-MULTIPRIME-FRT PCR [50]	N/A^b^	N/A^b^
Chlamydia	Vaginal specimen	AmpliSense *N. gonorrhea*/*C. trahomatis*/*M. genitalium*/*T. vaginalis*-MULTIPRIME-FRT PCR [50]	100% (73.3–100%)	100% (98.1–- 100%)
*Mycoplasma genitalium*	Vaginal specimen	AmpliSense *N. gonorrhea*/*C. trahomatis*/*M. genitalium*/*T. vaginalis*-MULTIPRIME-FRT PCR [50]	76.5% (50.1–93.0%)	100% (98.1–100%)

^a^CI confidence interval

^b^N/A estimates are not available for vaginal specimen samples

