### Challenges and limitations

Our study design uses several tools for reducing biases. Cluster randomization methods may offset the effects of selection bias, and analyses will compare baseline characteristics of both treatment and control arms. Our assessment measures include sensitive information on highly stigmatized behaviors, including sexual behavior history and drug use. We recognize the risk of reporting bias in these assessments, and have taken measures to minimize the risk of this, including establishing trust through the informed consent process and the use of CASI, which allows participants privacy and anonymity as they complete the survey measures. Finally, given the long time frame of our study and the staggered start dates between the Temirtau and Almaty sites, we suspect that external confounding factors may influence participant enrollment and intervention outcomes. For example, we have already observed a rapid contraction of Kazakhstan’s economy and a currency devaluation in the summer of 2015, which may impact participants’ savings behavior.

We expect several challenges in recruitment and retention of participants. FSW who use drugs are highly marginalized, and often hesitant to seek healthcare and other services for fear of stigma or legal repercussions [5]. Our decision to recruit at field locations as well as through a peer-referral system was intended to extend the reach of our study to as many FSW as possible. However, there is some evidence that shows that network-based recruitment and venue-based recruitment of FSW yields populations with different sociodemographic characteristics and even different STI prevalence [35]. We aim to resolve this issue through random assignment to study condition, and to conduct analyses that consider recruitment source, and any other differences potentially identified between study conditions, as a moderating variable.

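### The protocol says any measurement bias shared by both arms cancels in the ICER; additive errors and errors in identical components do, but proportional errors do not

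*Protocol article*

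**What the plan says.** The section on cost-effectiveness analyses defines the ICER as (Ci − Cj)/(Eik − Ejk), formed "by comparing extra cost with extra effectiveness in paired combinations". It then claims a protective property for this form: "This approach safeguards validity against any biased measurements of cost or effectiveness that are common to both" treatments, "because they cancel out". The claim is not limited to any type of error. The section presents the ratio as one that policymakers can set directly beside figures they already hold.

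On effectiveness, the section says: "Cost-effectiveness of the intervention will be analyzed based on STI infections and number of HIV and HCV cases averted over the 12-month period". Transmissions averted are to be built from "a Bernoulli Process Model, the difference in risk-behavior frequencies times HIV transmission probabilities per act". On robustness, it says: "One-way sensitivity analyses will use a range (e.g., 95% CIs) of HIV and HCV rates in the target population".

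Two other places bear on measurement error. Table 2 (Assessments) gives the M. genitalium assay sensitivity as "76.5% (50.1–93.0", that is, 76.5% with a 95% CI of 50.1% to 93.0%. Under Challenges and limitations, the article says of the self-reported measures: "We recognize the risk of reporting bias in these assessments".

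**The concern.** Differencing removes what is added equally to both arms. It does not remove what multiplies both arms, because the multiplier stays in the difference. An assay that misses a share of infections acts as a multiplier. So, approximately, does under-reporting of risk acts by a common fraction, and so does a proportional error in unit costs.

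The consequence is one of scale. Comparing an ICER with figures from other programmes requires its absolute level to be right. A factor common to both arms leaves the sign of the effectiveness difference unchanged but shifts that level. A reader who accepts the sentence as written would see no need to ask how far the ratio could be displaced.

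**Working it through.** The protocol states no ICER and no size of bias, so there is no figure to reproduce. The check is algebra on the stated formula, with the protocol's own inputs where they exist.

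**Additive and proportional error in effectiveness.** The power section assumes STI incidences of 0.144 (HIVRR) and 0.043 (HIVRR+MF), a difference of 0.144 − 0.043 = 0.101.
- Additive error a: (0.144 + a) − (0.043 + a) = 0.101 for any a. With a = 0.02 this is 0.164 − 0.063 = 0.101, and the ICER is unchanged.
- Proportional error f: f × 0.144 − f × 0.043 = f × 0.101. With f = 0.765 this is 0.0773, and the ICER is multiplied by 0.101/0.0773 = 1/0.765 = 1.31.

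**Costs.** Per woman, write Cj = H (the HIVRR sessions) and Ci = H + M (HIVRR plus MF).
- Error c on H alone: (cH + M) − cH = M, so it cancels, although it is proportional.
- Error c that also falls on M: (cH + cM) − cH = cM, so the ICER is multiplied by c. For example, c = 1.2 raises it by 20%.

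**Assay sensitivity (Table 2), for effectiveness based on test results.** The observed difference is the true difference × (Se + Sp − 1). With specificity at 100% the factor on the ICER is 1/Se.

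| Infection | Point estimate | Lower CI limit of Se |
|---|---|---|
| M. genitalium | 1/0.765 = 1.31 | 1/0.501 = 2.00 |
| Chlamydia | 1.00 | 1/0.733 = 1.36 |
| Syphilis | 1.00 | 1/0.991 = 1.01 |
| HCV | 1.00 | 1/0.9479 = 1.05 |
| HIV | 1/0.999 = 1.00 | 1/0.994 = 1.01 |
| Gonorrhea, trichomoniasis | no sensitivity given | – |

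The upper limit for M. genitalium gives 1/0.930 = 1.08. Using the tabulated specificities of 99.8% (HIV) and 99.88% (HCV) changes their point factors only to 1.003 and 1.001.

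**Five-STI composite.** Let s be the share of averted infections that are M. genitalium only, and suppose the other four assays miss none (both are assumptions). The factor is 1/(1 − 0.235s).
- s = 0.2 gives 1.05; s = 0.5 gives 1.13; s = 0.75 gives 1.21.
- Reaching 1.3 needs s = (1 − 1/1.3)/0.235 = 0.98.
- With M. genitalium sensitivity at its lower limit of 0.501, the factor is 1/(1 − 0.499s), or 1.11 to 1.60 for s = 0.2 to 0.75.

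**Under-reported acts, for modelled infections averted.** The documents give no reported fraction, so 0.5 to 0.9 is assumed, equal in both arms.
- Linear form, as the section words it: 1/0.9 = 1.11, 1/0.8 = 1.25, 1/0.7 = 1.43, 1/0.5 = 2.00.
- Non-linear Bernoulli form, risk = 1 − (1 − p)^n, with illustrative p of 0.001 to 0.01 and 100 v 50 or 40 v 20 acts: a fraction of 0.9 gives 1.03 to 1.11, 0.765 gives 1.10 to 1.30, and 0.5 gives 1.38 to 1.97. Inflation is below 1/f in every run but does not vanish.

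**The case against.** The strongest reply is that the sentence is loosely worded rather than wrong in substance, and that the sizes are small. Much of this stands.

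- **Costs.** All women receive the same four HIVRR sessions, so any error in that cost cancels, whether additive or proportional. This is a natural reading of cost errors common to both treatments. The claim fails only for error that also reaches the MF costs.
- **Size.** A reader might infer from the 76.5% sensitivity that the ICERs are out by 1.3-fold or more on the plan's own figures. The documents do not support that. The factor of 1.31 belongs to M. genitalium alone, at its point estimate, and its interval reaches down to 1.08. The section names no separate ICER for that infection. HIV and HCV are essentially unaffected by assay sensitivity.
- **Reporting bias.** The limitations section acknowledges a risk. It does not say that acts are under-reported, that the error is proportional, or that it is equal in the two arms. Any size is an assumption.
- **Sensitivity analysis.** A reader might infer that it covers HIV and HCV rates because the authors relied on cancellation. The text does not link the two statements and does not say that no other analysis will be done. A journal article may leave the full list to the fuller plan.
- **Direction.** Missed infections and under-reported acts make the ICER too high, which is conservative for the intervention. That holds for these two errors. It does not hold for understated MF costs, and it does not make the level correct for outside comparison.

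None of this rescues the general claim for effectiveness. The article positively states a property that the formula lacks; this is not a detail left for a later document.

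**Conclusion.** The cancellation claim is wrong as written and should be narrowed. It is true for additive errors and for errors in components identical in both arms. It is false for proportional errors in effectiveness and for proportional errors that reach the MF costs.

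The size depends on the outcome. Only the assay sensitivities and their intervals come from the protocol. The composite range rests on an assumed M. genitalium-only share and on the other assays missing no cases, which cannot be checked for gonorrhea and trichomoniasis. The under-reporting range rests on assumed fractions, equal between arms. The assay factors apply only where effectiveness is taken from test results, since assay sensitivity is not a stated input to the behaviour-based model.

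The average ratio Ci/Eik, which the section also reports, has no differencing, so not even an additive error cancels there. The cancellation sentence refers to the ICER, however, and makes no claim about the average ratio.

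The point concerns a secondary aim. The ICER formula itself is sound, and no primary estimate, test or sample size is affected.

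**What to change.** Restate the property along these lines: *errors that add the same amount to both arms, and errors in components identical in both arms such as the HIVRR session cost, cancel in the ICER; proportional errors in effectiveness or in the MF costs do not.*

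Add one-way sensitivity analyses:
- **Test-based outcomes.** Correct each infection by its own Table 2 sensitivity over its confidence interval. Do not apply the M. genitalium value to other infections or to the composite; build the composite from the infection-specific corrections. Where Table 2 gives no sensitivity, state an assumed range.
- **Modelled infections averted.** Vary the fraction of acts reported (for example 0.5 to 1.0, labelled as an assumption) and re-run the Bernoulli model at each value. Dividing the result by the fraction would overstate the correction.
- **Costs.** Vary the MF unit costs proportionally.

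Report the resulting ICER ranges for STIs as well as for HIV and HCV. The cost is one rewritten sentence, a few extra runs of the cost-effectiveness calculation, and a wider stated ICER range. No new data are needed.
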